### Outcomes

The primary outcome will be the caries increment measured both at enamel and dentinal levels. The secondary outcomes will be the differences obtained comparing caries increment and the variation of plaque pH in relation to the treatment used. Furthermore, a cost-effectiveness analysis will be performed using as outcome the measurement of quality-adjusted life years (QALY) [21].

### Participant timeline

The study should have been recruiting patients from August 2021 to September 2021; nevertheless, as previously described, COVID-19 does not allow at the moment to make predictions about it. Each subject will be enrolled for 36 months, estimating 9 months (one school year) of treatment and 27 months of follow-up. The study phases are presented in Fig. 2.

**Fig. 2 Fig2:**
[figure not shown]
The study phases

### Recruitment

The recruitment will occur in Zanskar Valley (Ladakh), in Padum city.

### Assignment of interventions

#### Allocation: sequence generation and concealment mechanism

The random list will be generated using a computer program (Microsoft Excel for Mac version 16.37); a school-class-based randomization will be carried out by [name] in permuted blocks of 2 or 4 classes with a random variation of the blocking number and 2 groups will be created [22, 23].

The two types of chewing gums will both be supplied in plain white containers coded as ‘green’ or ‘blue’. The code will be sealed by an independent monitor and not broken until the statistical analysis will be finalized.

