### Participants, interventions and outcomes

#### Setting

The study will be conducted in the Zanskar Valley (Ladakh). School classes of subjects aged 5–14 years old will be randomly selected from a list of classes in the selected schools.

In 2018, the total schoolchildren population in the Zanskar Valley aged 5–17 years amounted to 2407 children.

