### Interventions

After obtaining actual caries data, schools with similar numbers of schoolchildren (at least 300 subjects per school) will be selected for the preventive project. The participants will be randomized, taking as cluster the school class, allocating each class into one of the two groups of the study (Fig. 1):

(1) The first group (Xyl) will receive sugar-free gums containing 70% (w/v) Xylitol as the only sweetener

(2) The second group (Pol) will receive reduced sugared gums containing 23% (w/v) Maltitol

Both groups of children will receive a total of 6 pellets of chewing gum a day during a period of one school year (about 9 months). All chewing gums will be produced and supplied by Perfetti Van Melle SpA (Lainate, Italy). All types of chewing gums will weigh 1.4 g each and will be identical in colour, shape and taste.

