#### Clinical examination

Clinical examination, coordinated by [name] as responsible of the coordinating centre, will comprise an oral examination (caries index, bleeding on probing recording) and an evaluation of plaque pH fluctuation after the sucrose challenge. Bleeding on probing will be used as a proxy of plaque presence, since there is a causal relationship between bleeding on probing and amount of plaque [13, 14].

The subjects will be examined using a mouth mirror, a ball-ended probe and artificial light. Caries registration will be performed with regard to the first and second primary, and first and second permanent, molars. The International Caries Detection and Assessment System (ICDAS) will be used to record caries at tooth level as initial, moderate or severe lesions, the number of filled teeth and the missing teeth for caries [15, 16]. Initial caries lesion can be defined as a primary lesion, which has not reached the stage of an established lesion with cavitation (ICDAS scores 1 and 2). Moderate caries lesions are defined as white or brown spot lesion with localized enamel breakdown or an underlying dentine shadow without visible dentine exposure (ICDAS scores 3 and 4). Extensive caries lesions are defined as a distinct cavity in opaque or discoloured enamel with visible dentine (ICDAS scores 5 and 6) [9, 15, 16]. The bleeding on probing score, as the percentage of periodontal site bleeding, will be registered in all subjects.

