#### Sample size

The sample size calculation was performed based on the primary outcome of the randomized clinical trial (caries increment at enamel and dentinal level). The calculation considered the results of a 3-year period [7, 8]. It was also taken into account an increment of approximately 10% of the sample due to some changes in the prevalence of the disease. Thus, estimating a level of significance of 0.05 with a power of 80% and a caries prevalence of about 90% [5], the number of participants was set to 409 subjects (Kelsey method), based on a 10% absolute difference between the groups, using a two-tailed test [19].

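### School classes spanning ages 5 to 14 are allocated in small blocks with no stated balancing by grade, age or school, and the named test of caries increment cannot adjust for an imbalance

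*Protocol article*

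**What the plan says.** The Interventions section makes the class the unit of allocation: "The participants will be randomized, taking as cluster the school class, allocating each class into one of the two groups of the study". Under Setting, classes of children aged 5 to 14 "years old will be randomly selected from a list of classes in the selected schools". Under Allocation, the list is produced by computer "in permuted blocks of 2 or 4 classes with a random variation of the blocking number and 2 groups will be created". That section gives the software, the unit, the block sizes and the random variation of block size. It names no stratum or matching factor, and no order in which classes enter the list.

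Under Clinical examination, "Caries registration will be performed with regard to the first and second primary, and first and second permanent, molars".

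The data analysis section tests group differences in caries increment with Mann–Whitney U. It also plans Kaplan–Meier graphs and Cox regression with shared frailty. It names no covariates for the Cox model, and does not say at which level the frailty is shared.

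**The concern.** A school class is usually close to a single age group. Blocks of 2 or 4 equalise the number of classes per arm. They do not equalise the grades of those classes unless the list is arranged so that neighbours are alike.

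Age matters here because both dentitions are scored over 36 months. A child's age largely settles which primary molars are present and about to be shed, which permanent molars have erupted, and how long they have been exposed. If one arm receives more of the younger classes, a difference in increment reflects dentition as well as the gum. A rank test on the increment cannot separate the two. Even without a visible imbalance, differences between grades add to the variation between classes and cost precision.

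Stratification cannot be added after allocation. The article reports that recruitment has not begun, so the allocation scheme can still be changed.

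**Working it through.** **The plan's own figure.** The inputs are in the Sample size section: "estimating a level of significance of 0.05 with a power of 80% and a caries prevalence of about 90"%, and "based on a 10% absolute difference between the groups, using a two-tailed test". Reading the contrast as 90% against 80%, the Kelsey formula gives

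n per arm = (1.960 + 0.842)² × 0.85 × 0.15 × 2 / 0.10² = 200.1,

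that is 201 per arm and 402 in all. The article states: "the number of participants was set to 409 subjects (Kelsey method"). The two agree within 2%. The stated allowance ("It was also taken into account an increment of approximately 10% of the sample due to some changes in the prevalence of the disease") would give about 440 instead (2 × 200.1 × 1.1), but this does not affect the present point. The figure of 409 is used below only to gauge the number of classes.

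**Number of classes (assumption).** Neither class size nor number of classes is given. With 20 to 30 enrolled children per class, 409/30 = 13.6 and 409/20 = 20.5, so about 14 to 20 classes. A range of 30 to 40 classes is shown as well.

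**Spread of the age difference.** Assume one age per class, ages spread evenly over 5 to 14, equal class sizes and random list order. The variance of ten equally likely whole ages is (10² − 1)/12 = 8.25, so the SD is 2.872. With K/2 classes per arm,

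SD(difference in mean age) = 2 × 2.872 / √(K − 1).

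This gives 5.745/√13 = 1.59 years for K = 14, 5.745/√19 = 1.32 for K = 20, 5.745/√29 = 1.07 for K = 30 and 5.745/√39 = 0.92 for K = 40. Simulation of the stated blocks gave 1.60, 1.31, 1.06 and 0.93.

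**Share of allocations with a given imbalance** (20,000 simulated allocations per row, random blocks of 2 or 4):

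| Classes | Random order, ≥1 year | Random order, ≥2 years | Grade order, ≥1 year | Grade order, ≥2 years |
|---|---|---|---|---|
| 14 | 59.8% | 21.5% | 11.7% | 0.5% |
| 16 | 56.1% | 20.8% | 6.6% | 0.0% |
| 18 | 51.5% | 14.4% | 3.9% | 0.0% |
| 20 | 49.8% | 14.6% | 3.2% | 0.0% |
| 30 | 38.5% | 5.8% | 0.1% | 0.0% |
| 40 | 30.8% | 3.4% | 0.0% | 0.0% |

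**Sensitivity.**
- If the ages of the selected classes are themselves drawn at random, the 1-year shares for 14, 16 and 20 classes are 54.6%, 50.6% and 45.8%. The 2-year shares are 20.8%, 17.7% and 12.8%.
- The normal approximation 2[1 − Φ(1/SD)] gives 53% for K = 14, 45% for K = 20, 35% for K = 30 and 27.7% for K = 40. It is a little lower because, with whole-year ages, some allocations differ by exactly 1 year. For 30 to 40 classes, about 27 to 39% covers both methods.

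**The case against.** Five points can be made on the other side.

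1. *Covariates may be listed elsewhere.* A reader might infer that no age or baseline adjustment is planned. The article does not support that. It names no covariates, but the Cox model could carry them, and a condensed article commonly leaves the list to an analysis plan. This stands. It does not help the Mann–Whitney test, which takes none, and no later analysis plan can supply stratification once classes are allocated.

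2. *Baseline status is partly handled.* The tooth is the unit of analysis, progression is defined from each starting stage, and the outcome is a net increment. A tooth-level Cox model counts only teeth at risk, so unequal numbers of molars do not by themselves distort the hazard comparison. This stands, but it does not remove differences in risk per tooth by age and tooth type.

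3. *The size rests on unstated facts.* Class number, one age per class and list order are all assumptions. On a grade-ordered list, small blocks already balance age well. This stands, and is why the result is given as a range. If a grade-ordered list is intended, the protocol should say so, because the balance depends on it.

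4. *Chance imbalance is not bias.* A reader might infer that the trial's estimate will be biased. Under valid randomisation it is unbiased in expectation. The cost is precision, and the risk that the one allocation used is confounded.

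5. *A power loss might be inferred.* The article gives neither an intraclass correlation nor a between-grade variance, so no power figure is offered.

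**Conclusion.** The point holds as a design weakness that should be corrected before allocation, not as an error that invalidates the trial. What is firm is that whole classes across a ten-year age span are allocated with no stated balancing by grade, age or school, and that the one test tied to the increment cannot adjust.

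How often a material age difference would arise depends on the assumptions. It is about an even chance or somewhat more for 1 year with 14 to 20 classes in random order, about a third with 30 to 40 classes, and uncommon if the list runs in grade order. The last case shows how much ordering or blocking by grade would gain.

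**What to change.** Before allocation, pair or block classes of the same or adjacent grade within each school. Use blocks of 2 where a grade band has few classes.

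Make the adjusted shared-frailty Cox model the between-group comparison. Set class as the frailty level, and include the school/grade stratum, the child's age and baseline molar caries as covariates. Keep the unadjusted Mann–Whitney test as supportive only. With perhaps 14 to 20 classes, keep the strata broad: a separate term for every pair would mean 7 to 10 strata.

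The cost is small: no extra children or visits, since class lists are needed for selection anyway, and age and molar caries are recorded at baseline. The downsides are that allocation within a pair is slightly more predictable, and that some blocks will be incomplete where a school has an odd number of classes in a grade band.

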### Implementation

All examinations of the children enrolled will be carried out by calibrated dentists. The clinical examination of the enrolled sample will be recorded at baseline (*t*_0_), will be repeated after 12 months since the start of the chewing gum administration period (*t*_1_), after another 12 months period (*t*_2_) and finally after further 12 months (*t*_3_) (24 months from the end of the chewing gum use) (Fig. 2).

### Blinding

The study will have a triple-blind design: children, parents/guardians and teachers responsible for the treatment; dentists who will evaluate the outcomes; and the statistician who will analyse data will be blinded to the allocation group of the participants.

### Data collection, management, and analysis

The follow-up assessments will be performed by calibrated blinded dentists. The clinical data will be recorded on electronic sheets organized on PageMaker and then transferred into Microsoft Excel Software. The data management team is formed by two authors ([name], [name]). Data will be cleaned, deleting those revealing the participants’ identities, and they will be shared in a public repository at the moment of the submission of the manuscripts.

Data on caries will be recorded considering the tooth as the unit of analysis. The progression or change of status can be described with three modalities: 1—as the change from no caries stage to initial stage or to moderate stage or extensive; 2—as the change from initial stage to moderate or extensive stage; and 3—as the change from moderate stage to extensive stage. The net caries increment for initial, moderate and extensive caries levels, using ICDAS (Δ-initial, Δ-moderate and Δ-extensive), will be calculated in primary and permanent molars. Differences between groups in terms of caries increment will be evaluated using the nonparametric Mann–Whitney *U* test. Data analysis will be conducted through Kaplan–Meyer graphs to evaluate caries increment. A comparison of the methods will be carried out with Cox regression with shared frailty. The calculation of sensitivity, specificity and accuracy will consider the results obtained with the indices and the classification of caries lesion presence by the proposed reference standard. The cost-effectiveness ratio will also be verified, considering as effectiveness the prevention of the primary outcome. For all tests, two-tailed analyses will be used, considering a level of significance of 5%. The quality-adjusted life-year index (QALY) will be calculated to assess the value of the preventive intervention [22]. To determine QALYs, the utility value associated with a given state of health by the years lived in that state will be calculated. A year of life lived with no caries increment will be worth 1 QALY (1 year of life × 1 utility value) [22, 23]. Plans to promote participant retention and completion of follow-ups will be performed; a list of any outcome in participants who discontinue the treatment will be compiled and the data will be analysed, taking into account that living conditions in Ladakh do not allow for high mobility of the population. This will make participant retention a minor problem.

The effectiveness of the treatment will be assessed for those who fully followed the protocol (per-protocol subjects). The efficacy and consequences of treatment will be also considered, calculating the event rate (ER) for each group and the number needed to treat (NNT) [24]. An event will be defined as the change of status at tooth level, i.e. the development of a new lesion or the progression of an existing lesion to a more severe level or the change of a tooth previously affected in a filled or a missing tooth during the 2-year follow-up period.

Analyses will be performed using the statistical package Stata 16.0 (Stata Corp, College Station, USA).

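### Classes are randomised, but the Mann–Whitney test named for caries increment ignores class, so its true error rate exceeds 5%; the level of the Cox frailty is not stated

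*Protocol article*

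**What the plan says.** Under Interventions, the protocol article randomises participants "taking as cluster the school class, allocating each class into one of the two groups of the study". The allocation section confirms this: classes are drawn "in permuted blocks of 2 or 4 classes with a random variation of the blocking number and 2 groups will be created". The Discussion defends a group-randomised design as suited to a school programme.

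The analysis text is in the section on data collection, management and analysis. It states that "Data on caries will be recorded considering the tooth as the unit of analysis" and, of the event, that "An event will be defined as the change of status at tooth level". Caries increment is the primary outcome under Outcomes. For it the plan says "Differences between groups in terms of caries increment will be evaluated using the nonparametric" Mann–Whitney U test. It adds Kaplan–Meier graphs and then "A comparison of the methods will be carried out with Cox regression with shared frailty". For all tests, "two-tailed analyses will be used, considering a level of significance of 5"%.

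School class is named in no analysis sentence. The plan does not say whether the Mann–Whitney test ranks teeth or per-child increments, which group shares the frailty, or which of the two methods decides the primary outcome.

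**The concern.** The data have three levels: teeth within children, children within classes, and treatment assigned to classes. Children in one class may resemble each other in caries increment for reasons unrelated to gum. The Mann–Whitney test takes its null variance from the number of observations, as if each had been allocated separately. With positive correlation inside classes, the real variance of the group difference is larger, so p-values come out too small.

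At stake is the efficacy claim. A chance imbalance between classes becomes more likely to be reported as a xylitol effect than the stated 5% allows. A test is named that does not fit the design the same article names, so this is not detail left to an analysis plan.

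**Working it through.** **1. The plan's own figure.** The Sample size section gives alpha 0.05 two-sided, power 80%, caries prevalence about 90%, a 10-point absolute difference and the Kelsey method, with a total of 409. Reading this as 90% versus 80% with equal arms:

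n per arm = (1.960 + 0.842)² × 2 × 0.85 × 0.15 / 0.10² = 7.849 × 0.255 / 0.01 ≈ 200.1, rounded up to 201, total 402.

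This is within 2% of 409. Adding the stated increment of about 10%, which the plan attributes to changes in prevalence, would give 402 × 1.1 ≈ 442. So 409 fits the formula for individually randomised children. No ICC, class size or design effect appears, and nothing in the sample size suggests that clustering was dealt with there.

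**2. Child-level Mann–Whitney test, class ignored.** Class size m and the ICC are assumptions.

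- Design effect: DE = 1 + (m − 1) × ICC
- True two-sided alpha of a nominal 5% test: 2 × [1 − Φ(1.96 / √DE)]
- Effective number of children: 409 / DE

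Example, m = 20 and ICC = 0.05: DE = 1 + 19 × 0.05 = 1.95; 1.96 / √1.95 = 1.404; alpha = 0.160; 409 / 1.95 ≈ 210.

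| m | ICC | DE | Effective children | True alpha, formula | True alpha, simulated |
|---|---|---|---|---|---|
| 20 | 0.01 | 1.19 | 344 | 7.2% | 6.4% |
| 20 | 0.02 | 1.38 | 296 | 9.5% | 8.9% |
| 20 | 0.05 | 1.95 | 210 | 16.0% | 15.5% |
| 20 | 0.10 | 2.90 | 141 | 25.0% | 23.9% |
| 25 | 0.01 | 1.24 | 330 | 7.8% | 7.8% |
| 25 | 0.02 | 1.48 | 276 | 10.7% | 9.8% |
| 25 | 0.05 | 2.20 | 186 | 18.6% | 16.8% |
| 25 | 0.10 | 3.40 | 120 | 28.8% | 27.0% |

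The simulated column applies an actual Mann–Whitney test to skewed, tied counts with no treatment effect (4,000 replicates; 20 classes of 20 or 16 classes of 25). With ICC zero the simulation returned 5.1% and 5.2%, so the excess comes from clustering.

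**3. Tooth-level Mann–Whitney test.** Further assumptions: 8 molars per child, 20 classes of 20, a four-level change score per tooth, and a latent correlation between teeth of one child of 0.2 or 0.4. The class share of that within-child component is set at 0, 0.02 or 0.05. Simulated alpha (2,000 replicates):

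| Within-child correlation | Class share 0 | 0.02 | 0.05 |
|---|---|---|---|
| 0.2 | 16% | 20% | 25% |
| 0.4 | 25% | 31% | 37% |

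Even with no class effect, ignoring the child alone gives 16% to 25%.

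**4. Cox model.** No error rate is computed, because the level of the frailty is not stated. Shared by class, it would carry the randomised unit. Shared by child alone, it would handle teeth within a mouth and still ignore class.

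**The case against.** The strongest reply is that the plan does not rely on the Mann–Whitney test alone. It also names a Cox model with shared frailty, which is a device for within-group dependence. The grouping variable is the sort of detail an article may leave to an analysis plan that is not shown here. That stands as far as the Cox model goes. A reader might infer that no between-group test respects the randomised unit, or that the frailty must belong to the child because the tooth is the unit. The document says neither, and a class-level frailty is compatible with its words.

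The reply does not rescue the Mann–Whitney test. It is the method expressly attached to group differences in caries increment, and nothing makes the Cox model the deciding analysis.

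A second reply is that the size is assumed. This also stands: class size, number of classes, ICC, teeth per child and within-child correlation are all absent. At ICC 0.01 to 0.02 a child-level test is off by roughly 1 to 6 percentage points, which is real but modest. A reader might take the tooth-level rates as the expected ones. The text makes the tooth the unit for caries data but does not clearly say that the rank test is run on teeth.

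A reader might also object to Cox regression because caries is seen only at annual visits, so event times are tied. That is a modelling preference. It has no bearing on the error-rate point and no harm from it was shown.

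**Conclusion.** Wrong as written for the Mann–Whitney test; unspecified, not shown to be wrong, for the Cox model.

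The direction needs only a positive class ICC. The size rests on assumptions: about 7% to 29% instead of 5% for a child-level test, and about 16% to 37% if teeth are ranked. An ICC near zero would be hard to presume. Children are aged 5 to 14, the outcome covers primary and permanent molars, and the allocation section describes no stratification by age or grade. If classes are formed by age, which is usual but not stated, classmates share which molars are present and at risk.

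It does not follow that every p-value for the primary outcome will be too small, or that a chance difference between classes will be declared an effect. The plan names two methods without saying which decides, and the inflation is a higher probability, not a certainty.

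**What to change.** State one primary comparison that respects class randomisation, and say that it decides the primary outcome. Two routes would do:

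- Keep the time-to-event model and specify a class-level frailty or random effect, with child also accounted for.
- Analyse a per-child increment in a model with a random effect for class.

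In either case add a small-cluster correction, or a permutation test that re-randomises classes in the way they were allocated. At 20 to 25 children per class, 409 children make only about 16 to 20 classes. Drop the plain Mann–Whitney test, or apply it only to class-level summaries. There is no need to abandon the time-to-event approach.

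The cost is a few sentences of analysis text, a little programming, and confidence intervals that are wider because they reflect the design. The Trial status section says recruitment has not begun, so the change can be made before any data exist.

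### Tooth status is seen only at yearly examinations, but the planned Kaplan–Meier and shared-frailty Cox analyses treat time as continuous, so the hazard ratio depends on an unnamed tie rule (minor)

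*Protocol article*

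**What the plan says.** The section Implementation sets the examinations. Following baseline (t0), the assessment "will be repeated after 12 months since the start of the chewing gum administration period", and t2 and t3 come one and two years later. Participant timeline agrees: "Each subject will be enrolled for 36 months, estimating 9 months (one school year) of treatment and 27 months of follow-up".

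The section Data collection, management, and analysis makes the tooth the unit and describes progression as a move from one caries stage to a worse one. The same section defines an event as a change of status at tooth level: a new lesion, progression, or a previously affected tooth becoming filled or missing.

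Three analyses of the increment are named there. The regression is given as "A comparison of the methods will be carried out with Cox regression with shared frailty". A rank test is planned as well: "Differences between groups in terms of caries increment will be evaluated using the nonparametric Mann–Whitney *U* test". The third analysis is the set of Kaplan–Meier curves for the increment.

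The abstract repeats the curves and the regression. The protocol names no grouped-time or interval-censored form, no rule for dating an event and no rule for ties.

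**The concern.** A tooth that is sound at t0 and carious at t1 changed at some unknown point in those 12 months. Its event time is interval-censored. Cox regression orders events by time and builds a risk set at each one. With only three examinations, nearly all the ordering is lost and each risk set contains many simultaneous events.

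The tie rule then decides what the model estimates: in effect a ratio of yearly risks (Breslow), a close approximation to the hazard ratio (Efron), or an odds ratio (exact partial likelihood). Entering actual calendar dates would split some ties, but the order would reflect when classes were visited and not when caries began. A child who misses t1 and is seen at t2 adds a further problem, because the change lies anywhere in 0–24 months but would be placed at 24.

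Cox is the only regression planned for the primary outcome. At stake is whether its hazard ratio can be read as one, and whether the same data could yield different answers with no rule fixed beforehand.

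**Working it through.** **Inputs.** Three follow-up examinations 12 months apart come from Implementation. The true hazard ratio of 0.70 is an assumption, chosen because it matches the plan's own contrast. Reading the sample-size statement as 90% v 80%, the Kelsey formula gives (1.96 + 0.8416)² × 0.85 × 0.15 × 2 / 0.10² = 200.1, so 201 per arm and 402 in total, near the stated 409. Taken as cumulative risks, 90% and 80% correspond to a hazard ratio of ln(0.20)/ln(0.10) = 0.699. The three-year tooth-level event rate P in the control arm is not in the document, so a range is shown. Yearly hazard is taken as constant, teeth as independent and attendance as complete.

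**Step 1: yearly risks.** Control: q0 = 1 − (1 − P)^(1/3). Xylitol: q1 = 1 − (1 − P)^(0.70/3).

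**Step 2: what each rule estimates in large samples.**

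- Breslow: setting d1 = d × n1·e^b/(n0 + n1·e^b) gives e^b = (d1/n1)/(d0/n0), which is q1/q0.
- Exact partial likelihood: the odds ratio [q1/(1 − q1)]/[q0/(1 − q0)].
- Efron: no closed form; solved numerically.
- Grouped-time complementary log-log: ln(1 − q1)/ln(1 − q0) = 0.70 exactly, whatever P is.

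**Step 3: worked case, P = 50%.** q0 = 1 − 0.5^(1/3) = 0.2063 and q1 = 1 − 0.5^(0.2333) = 0.1493. Breslow: 0.1493/0.2063 = 0.724. Exact partial: (0.1493/0.8507)/(0.2063/0.7937) = 0.675.

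**Step 4: range.**

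| P over three years | Breslow | Efron | Exact partial | Grouped-time |
|---|---|---|---|---|
| 10% | 0.704 | 0.700 | 0.696 | 0.700 |
| 25% | 0.710 | 0.700 | 0.690 | 0.700 |
| 30% | 0.712 | 0.700 | 0.687 | 0.700 |
| 50% | 0.724 | 0.701 | 0.675 | 0.700 |
| 70% | 0.741 | 0.702 | 0.657 | 0.700 |
| 90% | 0.776 | 0.709 | 0.616 | 0.700 |

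The event definition refers to a two-year follow-up period, against 36 months of enrolment. If that left only two examinations, the 90% row would become 0.809, 0.719 and 0.573 for the three tie rules.

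**Step 5: direction of the Breslow test.** Breslow's model-based variance for one interval is 1/d0 + 1/d1. The binomial variance of the log risk ratio is (1 − q0)/d0 + (1 − q1)/d1, which is smaller. The true spread is therefore between √(1 − q0) and √(1 − q1) times the reported standard error: 0.98–0.99 at P = 10%, 0.89–0.92 at 50%, 0.68–0.76 at 90%. The estimate is pulled towards 1 and the standard error is too large, so the test is conservative.

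**Step 6: where might P lie?** The only rate in the plan is "a caries prevalence of about 90" per cent. It comes from a survey in which about 10% of children had no dentinal lesion, so it is a proportion of children at one time, not an incidence among teeth. As an illustration, if 90% of children did have an event within three years and each had eight independent molars at risk, the tooth-level rate would be 1 − 0.1^(1/8) = 25%. Correlation within a child would raise that figure. So would the broad event definition, which includes initial enamel lesions, if it put more than 90% of children at an event.

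**The case against.** The best defence is that tie handling, event dating and missed visits are details an article may leave to an analysis plan. That is right for the tie rule taken alone, and its absence is not the finding. What stands is that the protocol, in two places, positively chooses continuous-time methods for an outcome seen once a year. An analysis plan that follows it inherits the mismatch.

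Four stronger readings are tempting, and the documents do not support them.

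- **Cox is invalid here.** With Efron ties and three examinations it stays within 0.01 of the true ratio across the whole table. The protocol does not say that Breslow or the exact partial likelihood will be used, nor does it state in words that the examination date is the event date.
- **The distortion is that of the 90% row.** That would treat a child-level prevalence as a tooth-level three-year incidence.
- **The primary comparison rests on Cox alone.** Cox is the only regression, but the Mann–Whitney test of the increment uses no event times, and the planned event rates and number needed to treat do not depend on ties either. The sample size is a two-proportion calculation.
- **The trial could falsely claim benefit.** Breslow errs towards no effect and makes the test conservative. The exact partial likelihood overstates the effect only if its odds ratio is read as a hazard ratio.

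The Kaplan–Meier part is milder still. With full attendance the curve is correct at each examination and is uninformative only in between. The protocol also expects retention to be a minor problem, which limits the missed-visit issue.

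**Conclusion.** The mismatch is real and the point is minor. The named methods do not fit an outcome known only within yearly intervals, and the hazard ratio will depend on a rule not fixed in this document. For a true value of 0.70 the spread across tie rules is about 0.01 at a 10% three-year tooth-level rate, 0.02–0.03 at 25–30%, 0.05 at 50% and 0.16 at 90%. Because the tooth-level rate is not given, the consequence may be negligible or material. The figures assume proportional hazards, constant yearly hazard, common visits and independent teeth. They isolate the tie effect and say nothing about the power of this trial, which has teeth within children within randomized classes.

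**What to change.** In the abstract and in Data collection, management, and analysis, replace the Cox sentence with a grouped-time proportional-hazards model: complementary log-log link, one record per tooth per examination interval, a separate intercept for each interval, and random effects where the shared frailty was planned. For a child who misses a visit, use the likelihood of the wider interval. Draw the curves as steps at t1, t2 and t3. If Cox is kept, state in advance that ties are handled by Efron's method. The two-year window in the event definition should be reconciled with the 36 months at the same time.

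The cost is wording only. The data and the hazard-ratio scale are unchanged, and recruitment has not begun. The one downside is a slightly longer model specification.
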